#### 2.10.2. Informational Bias

(1) Recall bias: the systematic bias due to the variation of accuracy and integrity when patients recall their previous therapy. (2) Reporting bias: patients are deliberately exaggerating or narrowing some information. (3) Detection bias: the collection of inaccurate information due to incomplete records and the error analysis. As for the method of control, detailed data collection and strict quality control methods will be developed; the information will be collected by objective indicators or methods; questionnaires should be designed strictly, and researchers should remain scientific [25].

#### 2.10.3. Confounding Bias

This bias will be controlled by (1) preventing confounding factors with restriction and match; (2) collecting detailed and accurate data that may include confounding factors; and (3) taking various measures in the stage of analysis with the methods of standardization and multivariate analysis.

### 2.11. Data Management and Monitor

#### 2.11.1. Data Management

Every participant should follow the instruction during the observational period, and their related information should be recorded and stored as a paper document (CRF). The electrical document should be stored in SPSS along with the procedure of filling in the paper document. All basic information of participants will be protected by the researching group, and a unique identified number will be applied during the procedure of follow-up. The informed consent will be stored in the office of Dongzhimen Hospital of Beijing University of Chinese Medicine along with the CRF.

#### 2.11.2. Monitor

A researcher from the researching group will be assigned as the clinical research coordinator (CRC) to assist experts in nonmedical judgment related affairs. CRC will compare the data between the paper and electrical document, and any modification of the data will be monitored and recorded in detail.

## 3. Discussion

The evaluation of clinical efficiency for modern western medicine paid close attention to the variation of laboratory indexes or pathohistological structure [26]. The evidence derives from objective and authentic results of human trials with rigorously designed, such as randomized controlled trials (RCTs) [27]. The distinguishing feature of dynamic, complicated, and multitarget effects for TCM cannot be reflected fully in the current evaluating system and model [10]. Clinical research of TCM should combine with the theory of evidence-based medicine, conducting the design and progress on the basis of syndrome differentiation of TCM and elucidating the result according to the element of TCM [28]. Evidence-based GAS is a method of evaluation combined with GAS and evidence-based medicine, which has the ability to objectively measure the individualized efficiency of TCM.

There are some obvious advantages of evidence-based GAS on the clinical application of TCM. Firstly, mutual communication in-depth between patients and physicians will be done to assist the construction of much more rational plan of TCM. Secondly, personal clinical experience and objective clinical evidence will be well combined to better show the character of TCM and promote to the whole world. Thirdly, this method primarily focuses on the dynamic and quantitative evaluation for TCM personalized treatment, which is much more suitable for TCM than standardized grouping evaluation.

Limitations for evidence-based GAS on clinical practice for observational research are listed as follows: (1) evidence-based GAS comes from the optimization of GAS, in which the process of evaluation is conducted according to the personalized intention of patients. Although evidence-based GAS combined with the evidence-based medicine of TCM and western medicine, the practicability and acceptability of it for personalized evaluation for TCM is still in at the centre of controversy; (2) working efficiency of researchers will be influenced on the basis of long-term observation and follow-up, and some of the events such as recall bias and follow-up bias cannot deal with appropriately; (3) although the clinical evidence from this observational study design can reflect the characteristics of individualized therapy for TCM, the evidence is still in a low level (II-3 level of the US Preventive Services Task Force [29]; C level of the Oxford Centre for Evidence-Based Medicine [30]) which needs further demonstration from experts.

## Figures and Tables

**Figure 1 fig1:**
[figure not shown]
Flow diagram of observational research by the evidence-based Goal Attainment Scale.

**Table 1 tab1:** The classification of score of weight for *Importance* and *Difficulty*.

Importance	Difficulty
0 = not important	0 = not difficult
1 = slightly important	1 = slightly difficult
2 = important	2 = difficult
3 = very important	3 = very difficult

**Table 2 tab2:** The goal of treatment from physicians and evidence-based medicine (3 to 5 goals among the 8 goals can be selected form the table).

Goal of treatment	Importance	Difficulty	Weight	Baseline	Results
1. Whether can improve the symptom of chest pain					
2. Whether can improve the quality of life (based on the SF-36 form)					
3. Whether can reduce the drug use					
4. Whether can reduce finical burden of patients					
5. Whether can improve prognosis of patients based on the report of MACE					
6. Whether can improve the physical-chemical indexes (blood lipids, vascular endothelial function, blood rheologic indexes, oxidative stress, blood routine, liver and kidney functions, and blood coagulation factor)					
7. Whether can improve imaging indexes (LVEF, chest radiography, CT, and MRI)					
8. Whether can improve syndrome efficiency of TCM					
9. Handwritten: the first goal of treatment that patients they want					
10. Handwritten: the second goal of treatment that patients they want					
*Sum of weight*					

**Table 3 tab3:** Scale for evidence-based GAS.

Scale for evidence-based GAS	−2	−1	0	1	2
					
1. Symptom of chest pain	Increase of the frequency of attack and the degree of pain, prolong for duration	No change of the frequency of attack, the degree of pain, and duration	A little bit relieves of the frequency of attack, the degree of pain, and duration	Obvious relieves of the frequency of attack, the degree of pain, and the duration	No any symptoms of chest pain

2. Quality of life based on SF-36 (^1^physiological function, ^2^physical function, ^3^body pain, ^4^general health, ^5^vitality, ^6^social function, ^7^emotional function, and ^8^mental health)	Aggravate obviously for 2 or more among the 8 dimensions of SF-36	No clearly improvement among the 8 dimensions of SF-36	Obvious amelioration for 1 to 2 among the 8 dimensions of SF-36	Obvious amelioration for 3 to 4 among the 8 dimensions of SF-36	Obvious amelioration for more than 4 among the 8 dimensions of SF-36

3. Situations of drug use	Obvious increase of dosage and categories	No obvious variations for dosage and categories	Decrease of dosage and categories (1 to 2)	Obvious decrease of dosage and categories (more than 2)	Discontinue drug followed by the doctor's advice

4. Financial burden	Obvious increase of financial input	No obvious change of financial input compared with before	Decrease of financial input and relieve of the burden	Obvious decrease of financial input and relieve of the burden	No financial burden

5. Prognosis of patients (MACE: ^1^death, ^2^MI, ^3^stroke, ^4^TIA, ^5^PCI, ^6^peripheral vascular intervention, and ^7^readmission)	1 or more new events (MACE) report compared with before	Events were observed similar to before and no new events report	No event (MACE) reports	No event (MACE) reports for a long time (six months to one year)	No event (MACE) reports for a long time (more than one year)

6. Physical and chemical indicators (^1^blood lipid, ^2^vascular endothelial function, ^3^blood rheologic indexes, ^4^oxidative stress, ^5^myocardial injure marker, ^6^liver and kidney functions, and ^7^blood coagulation factor)	Obvious aggravated more than 2 indicators	No obvious change compared with before	Amelioration of 1 to 2 indicators compared with before	Amelioration of 3 to 4 indicators compared with before	Amelioration of more than 4 indicators compared with before

7. Imaging indexes (^1^LVEF, ^2^chest radiography, ^3^CT, and ^4^MRI)	Obvious aggravated more than 2 indexes	No obvious change compared with before	Amelioration of 1 to 2 indexes compared with before	Amelioration of 2 to 3indicators compared with before	Amelioration of more than 3 indicators compared with before

8. Efficiency of TCM syndrome [13]	Obvious aggravated of the TCM syndrome compared with before	No obvious variation of the TCM syndrome compared with before	A little bit amelioration of the TCM syndrome compared with before	Obvious amelioration of TCM syndrome compared with before	Enormous amelioration of TCM syndrome compared with before

9. Handwriting: the goal 1 that patients want to achieve)					

10. Handwriting: the goal 2 that patients want to achieve					

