## 2. Methods

### 2.1. Objectives

The objective of this research is to evaluate the individualized clinical efficacy of TCM in the quantitative way (evidence-based GAS) by long-term observing the variation of symptoms and the corresponding adjustment of prescriptions after the individualized treatment of TCM on NSTE-ACS.

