#### 2.7.3. Situations of Drug Use

The drug contains the application of TCM and western medicine. The situation of drugs for TCM and western medicine will be measured by types, dosage, frequency, duration, and side effects. It should be highlighted that the reasons for the change of drug should be recorded clearly. The application of drugs should follow the medical advice of doctors strictly.

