#### 2.8.3. Judgment between Adverse Events and Drugs

(1) Whether there is a reasonable relationship between the time of TCM individualized treatment and suspicious adverse reactions. (2) Whether the suspected adverse reactions are consistent with types of adverse events that are already known for TCM individualized treatment. (3) Whether suspected adverse reactions can be reduced and disappear on the basis of drug withdrawal and dosage reductions. (4) Whether the same reaction occurs again after using the same drug. (5) Whether the suspected adverse reactions can be explained by the pathological status, combination of drugs, and previous therapy of patients.

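### Goal 3 (drug use) credits any reduction or physician-advised stop whatever the reason, so a withdrawal for a suspected adverse reaction can be recorded as efficacy

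*Protocol article*

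**What the plan says.** Table 2 words goal 3 as "Whether can reduce the drug use". Its scale in Table 3 runs from -2, "Obvious increase of dosage and categories", through -1, "No obvious variations for dosage and categories", then 0 for a decrease of one or two and +1 for an obvious decrease of more than two, to +2, "Discontinue drug followed by the doctor's advice".

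Section 2.7.3 sets the scope: "The drug contains the application of TCM and western medicine". It lists side effects among the things to be measured and asks that "the reasons for the change of drug should be recorded clearly". Neither side effects nor reasons appear in any level of goal 3.

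Other sections bear on the point:
- 2.8.3, on causality of adverse events, asks "Whether suspected adverse reactions can be reduced and disappear on the basis of drug withdrawal and dosage reductions", so withdrawals and reductions for suspected reactions are foreseen.
- 2.8.4 expects adverse reactions to be watched for while efficacy is being evaluated with the scale, and to be recorded during hospitalization and follow-up.
- 2.3.3 lets the physician take a patient out for allergic reactions, serious adverse events or complications.
- 2.6.4 treats reaching level 0 as success.
- 2.1 includes in the objective "the variation of symptoms and the corresponding adjustment of prescriptions after the individualized treatment of TCM on NSTE-ACS".

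**The concern.** Goal 3 reads direction of change only. A drug stopped because the patient improved and a drug stopped because it was suspected of doing harm receive the same score, and that score is at least the level that 2.6.4 counts as success. Safety information that the study already collects then enters the efficacy score with a favourable sign.

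The pooling of TCM with western medicine has a second effect. Section 2.6.2 takes the baseline before therapy, and 2.4 asks patients who need treatment to use TCM or combined therapy. A marked expansion of TCM after baseline can therefore pull goal 3 down, although adjustment of prescriptions is part of what the objective sets out to observe.

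This matters because T is the patient's final score (2.6.5), and the results of the scale are the only outcome for which 2.9 names an inferential analysis.

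**Working it through.** The protocol gives no figure to reproduce here, so the check is the size of the score change that the wording of goal 3 allows.

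**Inputs**
- Formula and p = 0.3: section 2.6.5.
- Baseline -1, three to five goals: section 2.6.2.
- Levels of goal 3: Table 3. The count of one or two at level 0 is taken to mean drugs.
- Assumption: equal weights of 1, with only goal 3 moving. Goal weights are otherwise set per patient (2.6.1).

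**Formula**

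Change in T = 10 × w₃ × (levels moved) / D. This is linear in the score, so it is the same whether T is computed from attained levels or from the difference from baseline.

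As printed, D = √(0.7Σw² + 0.3Σw²) = √Σw², which is √n at equal weights of 1. As a sensitivity assumption, let p multiply (Σw)². Then D = √(0.7n + 0.3n²), which is √4.8, √7.6 and √11 for n = 3, 4 and 5.

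**Results at equal weights**

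| Move on goal 3 | D used | n = 3 | n = 4 | n = 5 |
|---|---|---|---|---|
| -1 to 0 (one or two drugs withdrawn) | printed | +5.8 | +5.0 | +4.5 |
| | sensitivity | +4.6 | +3.6 | +3.0 |
| -1 to +2 (a single stop read as +2) | printed | +17.3 | +15.0 | +13.4 |
| | sensitivity | +13.7 | +10.9 | +9.0 |
| -1 to -2 (obvious expansion of TCM) | printed | -5.8 | -5.0 | -4.5 |
| | sensitivity | -4.6 | -3.6 | -3.0 |

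For example, 10/√3 = 5.8, 30/√3 = 17.3 and 30/√11 = 9.0. If goal 3 has weight 3 and the others weight 1, the move from -1 to 0 adds 30/√11 = 9.0 with three goals and 30/√13 = 8.3 with five (printed formula).

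**Effect on the patient's overall result (printed formula, equal weights)**
- Level 0 reading: the credit for one withdrawal exactly cancels a one-level worsening on one other goal. With three goals, if both others fall from -1 to -2, T still falls, by (1 - 1 - 1) × 10/√3 = -5.8.
- +2 reading: with both others falling to -2, T rises by (3 - 2) × 10/√3 = 5.8. With four goals the net change is 0, and with five it is -4.5.
- Goal 3 at -2 while all other goals reach 0: T rises by 5.8, 10.0 and 13.4 for three, four and five goals. With goal 3 at weight 3 and three goals, T falls by (3 - 2) × 10/√11 = 3.0.

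**The case against.** The strongest reply is that the scale is ordered. Because +2 lies beyond a decrease of more than two, it more naturally means stopping drug treatment than withdrawing one drug. A reader might infer that any drug stopped for toxicity earns +2. The wording permits that, but the order of the levels points to level 0 for one or two drugs, which is a third of the gain. This stands, and the level 0 figures are the ones to lead with. It does not remove the fault, because level 0 is still defined as success.

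Second, the exit rule in 2.3.3 may remove some patients with reactions before they are scored. That narrows the problem. Exit is the physician's decision, however, and 2.8.4 expects reactions to be noted during efficacy evaluation, so patients with reactions can remain and be scored. Neither section gives a scoring rule.

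Third, a reader might infer that starting or adding TCM always scores -2. Table 3 does not say so: -2 needs an obvious increase of dosage and categories, the word obvious has no threshold, and one extra prescription or a substitution may not meet it.

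Fourth, a reader might infer that T as a whole rewards harm and moves against TCM exposure. Goal 3 is one optional goal among the three to five chosen, and the other goals can offset it, as the working shows.

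Finally, reducing drug use is a goal agreed by physician, patient and family. For someone who chose it, more drugs of any kind does mean the goal was not attained. That is a fair defence of keeping TCM within the goal. It does not defend crediting a withdrawal made because of a reaction.

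**Conclusion.** The point holds for patients who choose goal 3. The scale credits a reduction or physician-advised stop whatever the reason, so a withdrawal for a suspected adverse reaction can be recorded as efficacy. At equal weights, baseline -1 and three to five goals, the credit is 5.8 to 4.5 T points on the natural reading (4.6 to 3.0 under the alternative denominator). If a single stop is read as +2 it is 17.3 to 13.4 (13.7 to 9.0). An obvious expansion of TCM can lower the score by 5.8 to 4.5 (4.6 to 3.0).

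The protocol does not say how often goal 3 will be chosen or how often drugs will be stopped for reactions, so the effect on the mean T across the 200 patients cannot be computed. The documents support a fault in the coding of one goal. They do not support the conclusion that T in general is inverted, or that the objective cannot be met.

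**What to change.** Reconcile 2.7.3, 2.8.4 and goal 3 of Table 3 before scoring:

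1. Use the reason for change already recorded under 2.7.3, so that a reduction or stop made because of an adverse reaction does not score above baseline on goal 3.
2. State whether +2 means stopping all drugs.
3. Tabulate TCM and western drug changes separately, by reason and over time, alongside T. This also serves the part of the objective that concerns adjustment of prescriptions.

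TCM can stay within the goal, and reductions for other reasons can still count. The change needs one row of Table 3, a sentence in 2.7.3 and a descriptive table, with no new data. It alters outcome coding only and no treatment decision. The small downside is that fewer drug reductions count toward goal 3.

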**Method:**

This is observational research with the prospective feature. A total of 200 patients will be recruited and observed in the three months by telephone or door visit, collecting the individualized intervention of traditional Chinese medicine and evaluating through the method of evidence-based Goal Attainment Scale. Participants will be included according to the inclusion and exclusion criteria. Any reasons for loss to follow-up and adverse events will be recorded strictly. *Discussion*. The evidence-based Goal Attainment Scale provides a personalized method of evaluation based on the Goal Attainment Scale and combined with evidence-based medicine, which can better reflect the characteristics and superiority of individualized and dynamic intervention for traditional Chinese medicine on the long-term prevention and treatment of non-ST segment elevation acute coronary syndrome than other methods of design. It is of great significance to explore and promote this method of design in the future.

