### 2.2. Study Setting and Trial Design

This is observational research which will conduct at the Dongzhimen Hospital Affiliated to Beijing University of Chinese Medicine (BUCM), the Third Affiliated Hospital of BUCM, and the Beijing Hospital of Traditional Chinese Medicine Affiliated to Capital Medical University. This research has a prospective feature, which means that the admission period of patients will be between March 1, 2020, and August 31, 2020. We will include 200 hospitalized patients who were diagnosed as NSTE-ACS. Each included patient will be followed up by telephone or door visit every 2 weeks, collecting the individualized intervention of TCM and evaluating through the table of evidence-based GAS. The whole procedure of the research will consist of 6 times of follow-up. This protocol conforms to the statement of Strengthening the Reporting of Observational Studies in Epidemiology (STROBE) [11] (see Supplementary File 2) and is made some adjustments based on the adaptability for TCM.

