#### 2.6.4. Expected Results

The expected result of every goal is generally defined as the level 0 for the most likely to occur after treatment based on the 5-level Likert scale (Table 3), and the realization of the expected result will constitute a successful one. The expected result specified by the goal can be as accurate as possible through the detailed setting of every indicator.

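### Table 3, goal 5 (MACE) does not fit the 12-week follow-up: levels +1 and +2 cannot be reached, and an event-free patient can be scored as a one-level success

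*Protocol article*

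**What the plan says.** **Follow-up.** The abstract has patients "observed in the three months by telephone or door visit". Section 2.2 gives the schedule: "Each included patient will be followed up by telephone or door visit every 2 weeks", and "The whole procedure of the research will consist of 6 times of follow-up".

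**Goal 5 anchors (Table 3, prognosis by MACE).**
- −2: one or more new events.
- −1: "Events were observed similar to before and no new events report".
- 0: no MACE reported, with no minimum duration.
- +1: "No event (MACE) reports for a long time (six months to one year".
- +2: "No event (MACE) reports for a long time (more than one year".

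**Scoring rules.**
- Section 2.6.2 places the baseline at −1 in general, with −2 reserved for some symptoms that have more room to improve. It has each patient use three to five goals, so goal 5 is optional.
- Section 2.6.4 makes level 0 the expected result and adds that "the realization of the expected result will constitute a successful one".
- Section 2.6.5 takes T from the difference between the baseline and result scores.
- Section 2.4 states that there is no control group and that patients serve as their own controls.

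**The concern.** Section 2.6.2 asks that goals be achievable and timed, and section 2.6.3 that the criteria for every score be clearly described. Goal 5 does not meet these requirements, in three ways.

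1. Its two upper levels need event-free periods longer than the study observes.
2. A patient entered at −1 who has no event fits level 0 as written. That patient can be credited with a one-level improvement at the first two-week visit. Nothing has improved; an event has merely not occurred, and there is no comparator to show what would have happened otherwise.
3. The −1 anchor also speaks of no new events, so two evaluators could score the same event-free patient differently, one recording no change and the other a success.

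The evidence-based GAS score is the study's central outcome and the subject of the repeated measures analysis in section 2.9. A scoring rule that can add points without a change in the patient, and that depends on the evaluator's reading, enters that analysis directly.

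**Working it through.** **1. Follow-up against the anchors.** From section 2.2: 6 visits × 2 weeks = 12 weeks = 84 days, or about 2.8 months. This agrees with the three months in the abstract. Level +1 starts at six months, about 183 days, and 84/183 = 0.46. Level +2 starts after one year, and 84/365 = 0.23. The study covers less than half of the first and less than a quarter of the second, so the best attainable score on goal 5 is 0.

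**2. Value of one level.** In the section 2.6.5 formula, moving one goal by one level changes the score by 10·w / D, where D is the denominator. As printed, D = √((1−p)Σw² + pΣw²), which reduces to √Σw², so p = 0.3 has no effect. In the usual GAS form, the second term is p(Σw)². Both are shown because the point holds under either. With n goals of equal weight:

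| Goals | Usual: 10/√(0.7n + 0.3n²) | As printed: 10/√n |
|---|---|---|
| 3 | 10/√4.8 = 4.56 | 5.77 |
| 4 | 10/√7.6 = 3.63 | 5.00 |
| 5 | 10/√11 = 3.02 | 4.47 |

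Example with every goal at −1 and only goal 5 moving to 0 (usual form): the score goes from 36.3 to 40.9 with 3 goals, and from 34.9 to 37.9 with 5. If goal 5 has weight 3 and the others weight 1, one level is worth 7.7 points (3 goals) to 6.2 (5 goals) in the usual form.

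**3. Effect of the cap.** With all other goals at +2, holding goal 5 at 0 lowers the maximum score from 77.4 to 68.3 (3 goals) or from 80.2 to 74.1 (5 goals), usual form. The cap acts in the opposite direction to the gain in step 2.

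**4. Net mean shift among patients who choose goal 5.** Let e be the proportion with an event. Event-free patients go from −1 to 0 (gain of one level) and event patients from −1 to −2 (loss of one level). The mean shift is (1 − e)d − e·d = (1 − 2e)d, where d is the value of one level. The documents give no event rate; I assume 5–15%.
- Lowest: e = 0.15, 5 goals: 0.70 × 3.02 = 2.1 points.
- Highest: e = 0.05, 3 goals: 0.90 × 4.56 = 4.1 points.
- With the printed denominator: 0.70 × 4.47 = 3.1 to 0.90 × 5.77 = 5.2 points.

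**5. Effect on the study mean.** Multiply by uptake, which the document does not give. If a quarter choose goal 5 (usual form): 0.25 × 2.1 = 0.5 to 0.25 × 4.1 = 1.0 points. For scale, the 95% CI half-width of a mean at n = 200, assuming SD 10, is 1.96 × 10/√200 = 1.4 points. The shift would equal that half-width at an uptake between 1.39/4.10 = 34% and 1.39/2.11 = 66%.

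**The case against.** The strongest reply concedes the unreachable levels and disputes the rest.

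- **The gain is not automatic.** If an event-free patient can fit both −1 and 0, an evaluator may leave the score at −1. The −1 anchor also has a first half, events similar to before, which a patient with no event arguably does not meet. This stands: the gain is possible, not guaranteed. The remaining defect is that the anchors do not decide the score.
- **The goal does respond to outcome.** A reader might infer that goal 5 measures nothing about treatment. The documents do not support that, because a new event scores −2. What is missing is attribution. That limit applies to every goal in an uncontrolled study, and the discussion itself grades the evidence as low. What is particular to goal 5 is that an absence of events, with no minimum duration, is worded as attainment of the expected result.
- **The cap cannot inflate efficacy.** Correct: it only lowers the attainable score. The cap and the gain are separate faults in one row.
- **The effect on the study may be small.** This also stands. Goal 5 is optional, weights vary, and at a quarter uptake the shift is below the illustrative 1.4-point half-width. A reader might infer that the study-wide mean is dominated by this row; that would need an uptake figure the document does not give.
- **MACE in other patients is not lost.** A reader might infer that an infarction in a patient who did not choose goal 5 disappears. It does not enter T through goal 5, but section 2.7.5 lists MACE as an outcome without limiting it to those patients, and section 2.8 covers the recording of adverse events.

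Nothing in the article extends follow-up beyond the sixth visit or counts event-free time before enrolment. Counting that time would sit badly with a baseline of −1 and would not reflect treatment during the study.

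**Conclusion.** The point holds. Goal 5 is wrong as written for a 12-week study: two of its five levels are out of reach, and level 0 lets event-free follow-up be scored as a one-level success that is not evidence of a treatment effect. The unclear boundary between −1 and 0 leaves the result to the evaluator.

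The cap follows from the document's figures alone. The value of one level (3.0 to 4.6 points, or 4.5 to 5.8 as printed) rests on equal weights. The net shift of +2.1 to +4.1 points among patients who choose the goal also assumes a 5–15% event risk, a baseline of −1, the usual denominator, and evaluators who score event-free patients at 0. The study-wide effect falls in proportion to uptake, to about 0.5 to 1.0 points at one quarter. The case for correction does not depend on these assumed rates, because the row mis-scores under its own definitions.

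**What to change.** Before scoring begins:

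1. Rewrite all five anchors of goal 5 so that each can be observed within 12 weeks.
2. Make −1 and 0 mutually exclusive, so that an event-free patient has exactly one possible score.
3. Set the baseline for this goal so that event-free follow-up alone is not scored as improvement.
4. Report the 12-week cumulative incidence of MACE with a 95% CI in all patients, whatever goals they chose.

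As an alternative to rewriting the row, present T with and without goal 5. Removing the goal from T altogether is possible but not required.

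The cost is one table row and one added analysis line. Section 2.7.5 already lists MACE as an outcome, but the article does not say that it is asked at every visit, so this should be confirmed. The downside is that goal 5 will show less gain than under the present wording.

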### 2.4. Interventions

This protocol is the observational setting with no controlled group. The method of self-control is used to compare therapeutic efficiency. All included participants will not apply any particular interventions for the aim of scientific research. The tool of evidence-based GAS is the way of analysis and evaluation, which represents patients who can receive the individualized treatment of TCM or western medicine based on their situations. The only requirement is they should choose the TCM or combined therapy if they have a need to be treated by physicians.

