#### 2.7.7. Imaging Indexes

The indexes will be collected and inquired including echocardiography (left ventricular ejection fraction, LVEF), chest radiography, chest tomography (CT), and magnetic resonance imaging (MRI).

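### Table 3 grades imaging (goal 7) by how many of four modalities improved, so the attainable score depends partly on which images routine care produced; goal 6 has a milder form of the problem

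*Protocol article*

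**What the plan says.** Table 3 fixes the levels of goal 7 as counts over four items: LVEF, chest radiography, CT and MRI.

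- Level 0: "Amelioration of 1 to 2 indexes compared with before".
- Level +1: "Amelioration of 2 to 3indicators compared with before".
- Level +2: "Amelioration of more than 3 indicators compared with before".

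Section 2.7.7 describes how the images are obtained: "The indexes will be collected and inquired including echocardiography (left ventricular ejection fraction, LVEF), chest radiography, chest tomography (CT), and magnetic resonance imaging (MRI". It sets no schedule and does not say that each patient has every modality. Section 2.4 describes an observational setting: "All included participants will not apply any particular interventions for the aim of scientific research". Section 2.2 places follow-up every two weeks, by telephone or home visit.

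Goal 6 (laboratory indicators) is also a count: level 0 is "Amelioration of 1 to 2 indicators compared with before", level +1 is "Amelioration of 3 to 4 indicators compared with before", and level +2 is more than four. Section 2.7.6 lists seven categories and says that they will be measured.

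Other rows work differently. Goal 8 is graded by percentage reduction from the patient's own pretreatment syndrome score (section 2.7.8), and goal 1 by degree of relief.

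**The concern.** Sections 2.6.3 and 2.6.4 define 0 as the expected result and +1 and +2 as better than expected. The Introduction justifies the Goal Attainment Scale on the ground that it keeps patients comparable although their indexes differ. A row that counts improved items, with no denominator for items measured and no regard to the size of change, works against both aims. The highest level a patient can reach is set in advance by how many items were imaged and could improve. A large and a small recovery in the same single measure receive the same score.

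Only LVEF among the four items is a quantity. For chest radiography, CT and MRI the article names a modality but not what is read from it.

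The row score enters the T score, which section 2.6.5 makes the patient's final score and section 2.9 analyses by repeated measures ANOVA. A ceiling on one row therefore carries into the main analysis for every patient who chose that goal.

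**Working it through.** The plan gives no figure on this point to reproduce. The check enumerates the Table 3 rules and puts the result through the formula in section 2.6.5.

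**Step 1. Ceiling on goal 7, by number of items that are followed and improve**

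| Items improved | Level |
|---|---|
| 0 | −1 |
| 1 | 0 |
| 2 | 0 or +1 (both definitions include 2) |
| 3 | +1 |
| 4 | +2 |

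More than 3 out of 4 can only be 4. With LVEF alone the ceiling is 0.

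**Step 2. Whether the plan secures four repeat images.** Section 2.7.7 gathers images without saying that all four are done, section 2.4 adds nothing to care for research purposes, and section 2.2 follows patients by telephone or home visit. None of the three provides for all four modalities at baseline and again later.

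**Step 3. Ceiling on goal 6.** If an indicator is a category (seven in total): 0 with one or two improvable categories, +1 with three or four, +2 with five to seven. If it is a single analyte, section 2.7.6 lists 4 + 3 + 1 + 2 + 5 + 5 + 4 = 24, and the ceiling all but disappears. The five myocardial injury markers alone could then give +2.

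**Step 4. Size in T points.** Inputs: p = 0.3 (section 2.6.5); 3 to 5 goals (section 2.6.2); all weights 1, the value section 2.6.1 sets when the physician sees no difference in weight. A loss of two levels on one goal is 10 × 1 × 2 / D = 20 / D.

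- As printed, both terms under the root contain the sum of squared weights, so D = √(0.7n + 0.3n) = √n.
- With the squared sum of weights in the second term, D = √(0.7n + 0.3n²).

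| Goals n | D, printed | 20/D | D, squared sum | 20/D |
|---|---|---|---|---|
| 3 | √3 = 1.732 | 11.5 | √4.8 = 2.191 | 9.1 |
| 4 | √4 = 2.000 | 10.0 | √7.6 = 2.757 | 7.3 |
| 5 | √5 = 2.236 | 8.9 | √11 = 3.317 | 6.0 |

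For scale, moving all n goals from the usual baseline of −1 to the expected 0 gains 10n / D. The two lost levels are 20 / 10n = 2/n of that gain under either formula: 67% with three goals, 40% with five.

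**Step 5. The overlap at two items.** It leaves one level undetermined, or 10 / D: 5.8 to 4.5 points as printed, 4.6 to 3.0 with the squared sum (3 to 5 goals).

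**The case against.** Several points on the other side stand.

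- **The goal is optional.** Patients and physicians choose three to five goals, which section 2.6.2 says should be achievable and realistic. Rows 9 and 10 are blank, so an LVEF goal graded by size could be handwritten. This limits how often the ceiling matters, but nothing allows the printed levels of row 7 to be rescaled for a patient.
- **Level 0 already counts as success.** With the usual baseline of −1, recovery of LVEF alone still registers as attainment. What is lost is the ability to record more than that.
- **The two-level gap is a worst case.** The patient who reaches +2 improved on three further items, so part of the gap reflects broader improvement.
- **Counting domains is a legitimate breadth measure.** Goal 2 does so with the SF-36. There, however, all eight dimensions come from one questionnaire, so every patient has the same denominator.

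A reader might infer that goal 6 is limited by tests ordered in the same way. The article does not support that: section 2.7.6 says the seven categories will be measured, and the sentence in section 2.4 concerns interventions, not measurements. Any ceiling there comes from how many categories have room to improve. Even that is an inference, because amelioration is undefined and a value can improve from within its normal range.

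A reader might also infer that the scale cannot measure change, or that differences between hospitals bias the result. Both go too far. The design is self-controlled, the article plans no comparison of hospitals, and a fixed ceiling limits gain without by itself creating change over time.

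**Conclusion.** The point holds for goal 7. Level +2 requires improvement on all four modalities, a patient with only LVEF followed is held at 0 or below, and two improved items have no unique level. The plan does not secure the imaging that the upper levels presuppose.

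With equal weights, the ceiling is worth at most 11.5 to 8.9 T points as printed, or 9.1 to 6.0 with the squared sum of weights. This applies to patients who choose goal 7 and is measured against a patient who improved on all four items. How many patients that concerns cannot be told from the article.

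For goal 6 the point is milder and conditional. It applies only if an indicator is a category, which the numbering in Table 3 suggests but does not settle. On the analyte reading the ceiling nearly vanishes, but the count still ignores size of change.

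This is a fault in two rows of an optional menu. It should be corrected, but it does not undermine the study as a whole.

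**What to change.** **Goal 7.** At baseline, name the imaging measure or measures that will be followed, LVEF where available. Grade −2 to +2 by size of change from the patient's own baseline, on the model of the percentage bands that section 2.7.8 uses for goal 8. Write the levels down before follow-up starts. Do not offer the goal where no imaging measure was taken at baseline. This also removes the overlap at two items.

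**Goal 6.** State whether an indicator is a category or an analyte. Then grade either by size of change in the named measures or by the share improved among those with room to improve at baseline.

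**Cost.** Two rows of Table 3 are reworded, and no extra tests are needed. The investigators have to set the cut-points, since the article offers none for imaging or laboratory change. Levels would be set per patient, which adds some evaluator judgement, as already happens for the handwritten goals; fixing them before follow-up limits this.
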